**Methods:**

VOYAGE is a prospective, randomized, multicenter controlled open label study designed to compare in terms of efficacy, efficiency, and safety a CMR aided/guided workflow to standard EAM-guided ventricular tachycardia (VT) ablation. Patients with an ICD or with ICD implantation expected within 1 month, with scar related VT, suitable for CMR and multidetector computed tomography (MDCT) will be randomized to a CMR-guided or CMR-aided approach, whereas subjects unsuitable for imaging or with image quality deemed not sufficient for postprocessing will be allocated to standard of care ablation. Primary endpoint is defined as VT recurrences (sustained or requiring appropriate ICD intervention) during 12 months follow-up, excluding the first month of blanking period. Secondary endpoints will include procedural efficiency, safety, impact on quality of life and comparison between CMR-guided and CMR-aided approaches. Patients will be evaluated at 1, 6 and 12 months.

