## Methods

### Study hypothesis and primary endpoint

Our hypothesis is that a comprehensive preprocedural individual characterization of the myocardial substrate via a CMR scan, and its integration within the mapping system can significantly improve technical intervention and patient outcome. The primary objective is to analyze the outcome of CMR guided/aided approaches of VT ablation in terms of effectiveness at 12 months in comparison to a control group (standard of care VT ablation). The primary endpoint is defined as any VT recurrences during a 12-months follow-up (not including the first month). VT episodes will be considered as recurrences if sustained (more than 30 s) or requiring appropriate ICD intervention and will be detected during outpatient clinic evaluation through an ICD interrogation.

Pre-specified group subanalyses will compare in terms of the primary endpoint:Patients with structural heart disease of ischemic originPatients undergoing endocardial-substrate only ablation

Secondary objectives are shown in Table 1.

**Table 1 Tab1:** Secondary endpoints

Secondary endpoints
Health-related quality of life changes
Procedural time (introducer in-introducer out)
Fluoroscopy duration
X-ray exposure
Radiofrequency time
Number of RF applications
VT inducibility at the end of ablation with number of residual VTs
Appropriate and inappropriate ICD interventions (ATP or shocks) anytime and after 1 month
Rate of patients with contraindication to CRM or with poor CMR imaging
Hospital admission for cardiac causes
VT storm anytime and after 1 month
Composite endpoint including death at any time, VT storm and appropriate ICD shock after 1 month of treatment
*Complications during 12-month follow-up*
Death (related or not to the procedure)
Myocardial infarction
Stroke or transient ischemic attack (TIA)
Other thromboembolic events
Cardiac perforation or tamponade
Vascular complications
Prolonged or repeat hospitalization
Heart block
Pericarditis requiring intervention
Pneumothorax
Pulmonary edema
Hepatic injury
Abdominal issues

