### Image processing

Images processing (ADAS 3D Galgo Medical, Barcelona, Spain) is pivotal to translate radiomics data produced by CMR into utilizable maps within the electrophysiology lab. Briefly, sequence packs created within each center will be transferred and processed by core-lab and finally elaborated by the software with the purpose of being integrated with the ablation mapping suite (CARTO 3, Biosense Webster, Diamond Bar, CA, USA). A pre-study phase for the achievement of quality standards in images acquisition has been accomplished in every center before the enrollment start date. The core-lab for image processing (U.O. Cardiologia 2—Azienda Ospedaliero Universitaria Pisana), will be further supported, if required, by Heart Institute in Teknon Medical Center (Barcelona, Spain). A VPN tunnel and an SFTP server will be used to securely transfer anonymized data between centers for post-elaboration.

LV endocardial and epicardial borders will be delimited by an experienced operator with a semiautomatic segmentation algorithm. Nine concentric layers will be identified from endocardium to the epicardium (10 to 90% of wall thickness). LGE-CMR information will be projected using trilinear interpolation over each layer surface and signal intensity distribution will be color-coded. Scar core (SC) and border zones (BZ) will be defined as 40% ± 5% and 60% ± 5% of maximum signal intensity respectively. Heterogeneous tissue channels (HTCs) will be defined as a corridor of BZ between two core areas or between a core area and a valvular annulus connecting two areas of healthy tissue.

The software will identify HTCs automatically, and they will be classified as:Sub-endocardial (layers from 10 to 50%).Sub-epicardial (layers from 60 to 90%).Transmural (layers from 10 to 90%).

Pixel signal intensity (PSI) maps and HTCs derived from LGE-CMR studies will subsequently be fused and aligned with the anatomical reconstructions extracted from multidetector cardiac tomography (MDCT) using the ADAS 3D software platform. This alignment allows the integration within the spatial reference coordinates of the mapping system by performing a fast anatomical mapping of the aortic root [9].

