### Ablation procedure

Ablation procedure will be carried out in an electrophysiology lab by using an electroanatomical mapping system (CARTO 3, Biosense Webster, Diamond Bar, CA, USA). An open irrigated 3.5 mm tip radiofrequency catheter (ThermoCool SmartTouch SF, Biosense Webster, Diamond Bar, CA, USA) will be used both for mapping and ablation.

In Groups 1 and 2 fast anatomical mapping (FAM) of the aorta from the aortic root to the origin of the left subclavian artery will be obtained in order to align such reconstruction with the MDCT-derived 3D model of the aorta and left ventricle, thus enabling the alignment between CARTO spatial references and post-processed CMR derived 3D model.

An electroanatomical map (EAM) of the target chamber will be obtained only in groups 2 and 3. EGMs will however be analyzed in all cases to avoid applications:At the level of His or fascicular EGMsAt the level of EGMs with an amplitude > 3 mV or 1.5–3 mV without delayed components, during sinus rhythm of after application of multiple extrastimuli to check for the presence of hidden slow conduction.

The target for RF ablation changes accordingly to the group of allocation or randomization.

Group 1: RF energy will be delivered at the entrance of HTCs identified in the maps created by images processing, regardless of the presence of any pathological electrogram (EGM) at such locations (Fig. 2). If VT is spontaneously induced, it’s allowed to map the circuit and ablate during tachycardia, even though it’s suggested to acquire the template and stop the arrhythmia (at first appearance) and continue the ablation of substrate.

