### Sample size and statistical analysis

To test the primary hypothesis, 103 patients will be necessary with 80% power and 5% type 1 error, considering 50% of group 1–2 (low risk), 50% of group 3 (high risk), 16% of likelihood of VT recurrences at 12 months in low-risk patients and 44% of likelihood in high-risk patients with HR (high risk/low risk of recurrences) of 2.75 (Cox PH, 2-sided equality).

All applicable statistical tests will be 2-sided and will be performed using a 5% significance level. Continuous variables will be reported as mean ± standard deviation, or median (range or interquartile range if data are skewed) if not normally distributed; these variables will be compared using Student’s t-test if normally distributed, Aspin-Welch test if normally distributed with unequal variance demonstrated using Variance-ratio F-test, or Mann–Whitney U test if not normally distributed. Categorical variables will be expressed as total number (percentage) and will be compared by chi-squared test. As far as the primary endpoint, data will be analyzed according to the intention-to-treat principle. Survival free from ventricular arrhythmia, will be evaluated using a time-to-first-event analysis with the Logrank test and the Kaplan–Meier cumulative event rate. A multivariable Cox proportional hazards model will be performed to investigate the effects of baseline characteristics in predicting ablation results.

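### The unadjusted tests fixed for continuous endpoints forgo precision in the randomised Group 1 vs Group 2 comparison that the baseline CMR, processed for every randomised patient, could supply

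*Protocol article*

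**What the plan says.** - **Randomisation.** Under Trial design, patients who cannot have CMR or CT, or whose images are not good enough to process, go to Group 3. The rest are randomised 1:1 to Group 1 or Group 2. Only these two groups are randomised.
- **Comparison.** The Abstract (Methods) lists among the secondary endpoints procedural efficiency and the "comparison between CMR-guided and CMR-aided approaches". Table 1 includes procedural time, radiofrequency time and number of RF applications.
- **Analysis.** Sample size and statistical analysis gives one rule for continuous variables: Student's "t-test if normally distributed, Aspin-Welch test if normally distributed with unequal variance demonstrated using Variance-ratio F-test", or a Mann-Whitney test if they are not normal. None of these takes a covariate. The only covariate model in the article is a Cox model for predictors of ablation results, which does not reach the procedural endpoints.
- **Baseline data.** Table 4 places the CMR of Groups 1 and 2 at baseline. Under Image processing, the core lab derives scar core and border zone from it, and HTCs are then found: "The software will identify HTCs automatically, and they will be classified as" one of three depth classes.
- **Link to the endpoints.** Under Ablation procedure, for Group 1, "RF energy will be delivered at the entrance of HTCs identified in the maps created by images processing". In Group 2 the CMR scar location directs the mapping, but electrograms decide where to ablate.

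**The concern.** Group 1 vs Group 2 is the one contrast in this trial that randomisation protects. The Discussion reports that shorter procedures with the guided approach rest so far on a single-centre, non-randomised study, so this contrast is the randomised test of that claim. It has only about half the planned patients.

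A patient with more channels and a larger scar can be expected to need more RF, most directly in Group 1, where channel entrances are the target. An unadjusted test leaves that between-patient variation in the error term. The information needed to remove part of it is already produced for every randomised patient. At stake is whether a moderate difference in procedure time, RF time or RF applications can be told apart from noise.

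**Working it through.** **1. The plan's own figure.** The article states that "103 patients will be necessary with 80% power and 5% type 1 error", with half the patients in Groups 1–2, recurrence of 16% and 44%, and HR 2.75.

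- Events (Schoenfeld) = (1.960 + 0.842)² / [0.25 × (ln 2.75)²] = 7.849 / 0.2558 = 30.7.
- Mean event rate = (0.16 + 0.44)/2 = 0.30.
- N = 30.7 / 0.30 = 102.3, rounded up to 103. The figure reproduces.

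**2. Patients in the randomised comparison.** 50% of 103 = 51.5, about 52, so n = 26 per group. This is a planning share, not a quota.

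**3. Unadjusted test.** Two-sided 5%, 80% power.

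- Normal approximation: (1.960 + 0.842) × √(2/26) = 2.802 × 0.2774 = 0.777 SD.
- Noncentral t with 50 degrees of freedom: 0.79 SD. Power for a true 0.6 SD difference is 56%.

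**4. Adjusted test with k = 2 covariates.** Let R² be the share of within-group outcome variance that HTC count and scar extent explain. The documents give no value, so a range is assumed. The variance of the group difference, relative to the unadjusted one, is

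(1 − R²) × (N − 3)/(N − 3 − k) = (1 − R²) × 49/47.

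The second factor charges for chance imbalance in the two estimated covariates. Degrees of freedom fall to 52 − 2 − 2 = 48. The last column is 52 divided by the variance ratio.

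| R² (assumed) | Variance ratio | Detectable difference, 80% power | Power at 0.6 SD | Equivalent unadjusted patients |
|---|---|---|---|---|
| Unadjusted | 1 | 0.79 SD | 56% | 52 |
| 0.10 | 0.94 | 0.77 SD | 59% | 55 |
| 0.20 | 0.83 | 0.72 SD | 64% | 62 |
| 0.30 | 0.73 | 0.68 SD | 70% | 71 |
| 0.50 | 0.52 | 0.57 SD | 84% | 100 |

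**5. Break-even.** The ratio equals 1 when 1 − R² = 47/49, so R² = 2/49 = 4%. Below that, adjustment gains nothing. At R² = 0 the detectable difference would be 0.81 SD, slightly worse than unadjusted.

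The table describes a linear model for a roughly normal outcome, possibly after a log transformation. For the count of RF applications it is a guide only.

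**The case against.** The strongest reply is that nothing here is wrong. Under 1:1 randomisation the unadjusted comparison is valid and unbiased, the sentence on tests is generic and never names Group 1 vs Group 2, and covariates for secondary endpoints are often left to the SAP. Most of this stands. However, the article does not leave the method open: it names unadjusted tests and offers no other for continuous variables. Their use in this comparison is inferred from the Abstract and Table 1, not spelled out.

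A second reply is that the benefit is undocumented. That also stands: R² is unknown, and at 10% the gain is slight. The case for a useful R² is the Group 1 targeting rule. It is weaker in Group 2, where electrograms choose the sites and other centre techniques are accepted.

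A third reply is that the covariates are not quite ready to use. The article does not name HTC count or total scar extent as recorded variables. Segmentation is semi-automatic with an operator, and the trial is open-label. Image quality is judged before randomisation, but full processing is not stated to be complete by then. This stands and shapes the fix.

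Stronger readings that a reader might infer are not supported:

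- *The comparison is biased by chance imbalance in scar.* Such imbalance is ordinary sampling error, already covered by the 5% level and the confidence interval.
- *A power claim is broken.* The article makes none for this contrast, and its remark in the Discussion on lack of power concerns long-term results.
- *Fluoroscopy time and X-ray exposure lose equally.* No rule in the article ties them to channel count.
- *Group 3 comparisons should be adjusted in the same way.* Group 3 has no processed map.

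**Conclusion.** The point holds as a matter of efficiency, not validity. The stated tests would leave the randomised comparison of procedure time, RF time and RF applications able to detect only about 0.79 SD with 80% power. Two covariates from images already processed would bring this to between 0.77 and 0.57 SD if they explain 10% to 50% of the variance, which is worth about 3 to 48 extra patients on a base of 52. The conclusion rests on three assumptions: the 50% planning share is met, R² exceeds about 4%, and the generic test rule governs this comparison. It is a worthwhile, inexpensive improvement to a secondary analysis and does not touch the primary endpoint.

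**What to change.** In Sample size and statistical analysis, add a rule for Group 1 vs Group 2:

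- **Procedure time and RF time:** the main analysis is a linear model, on the log scale if skewed, with group, HTC count and total scar extent (core plus border zone).
- **Number of RF applications:** a negative binomial model with the same terms.
- **Standard errors:** robust in both models, in a form suited to small samples, because HTC count may relate to RF use differently in the two groups. A group-by-covariate term can be a sensitivity analysis.
- **Covariates:** taken from the core-lab processing and either fixed before randomisation or read blind to allocation.
- **Reporting:** the adjusted difference or ratio with its 95% CI, with the unadjusted test kept as supportive.

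The cost is two degrees of freedom, two values per randomised patient extracted from existing maps, and a short procedure to lock those values or blind their reading. No extra patients, scans or procedures are needed. If the covariates prove uninformative, the loss is about 0.02 SD in the detectable difference (0.81 against 0.79).

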### Ablation procedure

Ablation procedure will be carried out in an electrophysiology lab by using an electroanatomical mapping system (CARTO 3, Biosense Webster, Diamond Bar, CA, USA). An open irrigated 3.5 mm tip radiofrequency catheter (ThermoCool SmartTouch SF, Biosense Webster, Diamond Bar, CA, USA) will be used both for mapping and ablation.

In Groups 1 and 2 fast anatomical mapping (FAM) of the aorta from the aortic root to the origin of the left subclavian artery will be obtained in order to align such reconstruction with the MDCT-derived 3D model of the aorta and left ventricle, thus enabling the alignment between CARTO spatial references and post-processed CMR derived 3D model.

An electroanatomical map (EAM) of the target chamber will be obtained only in groups 2 and 3. EGMs will however be analyzed in all cases to avoid applications:At the level of His or fascicular EGMsAt the level of EGMs with an amplitude > 3 mV or 1.5–3 mV without delayed components, during sinus rhythm of after application of multiple extrastimuli to check for the presence of hidden slow conduction.

The target for RF ablation changes accordingly to the group of allocation or randomization.

Group 1: RF energy will be delivered at the entrance of HTCs identified in the maps created by images processing, regardless of the presence of any pathological electrogram (EGM) at such locations (Fig. 2). If VT is spontaneously induced, it’s allowed to map the circuit and ablate during tachycardia, even though it’s suggested to acquire the template and stop the arrhythmia (at first appearance) and continue the ablation of substrate.

**Fig. 2 Fig2:**
[figure not shown]
Mapping suite showing a CMR-guided procedure, with VT interruption during RF delivery at an heterogeneous tissue channel **(**HTC**)** on 3D CMR model. Green: MDCT-derived aorta 3D model, blue areas: healthy tissue, red areas: scar tissue, yellow areas: border zone

Group 2 and Group 3: Ablation sites will be identified after analyzing the complete EAM, targeting conducting channel entrance-compatible EGMs, according to the “scar dechanneling” technique [10]. Other techniques aimed at achieving complete substrate ablation and currently used by the centre performing VT ablation, will be accepted. In case of absence of electrograms with delayed components at EAM, VT will be induced, and mapping will be done to delineate the circuit. In Group 2 the scar area localization via CMR images integrates the EAM data to help in substrate delineation focusing on that area. In Group 3 a complete left ventricle EAM will be achieved.

At the end of ablation, we will verify the absence of pathological EGMs and we’ll proceed towards inducibility test. In case of VT induction, we could have 2 scenarios: (1) hemodynamically tolerated VT: it will be mapped and ablated; (2) not hemodynamically tolerated VT: VT template will be taken and, after its interruption, used for pacemapping to identify VT exit site, which will undergo ablation.

Acute success will be defined as non-inducibility (2 drives, 2 sites, up to 3 extrastimuli) of any sustained monomorphic VT at the end of the procedure. Partial success will be considered with the clinical VT successfully ablated with other monomorphic VTs remaining inducible. Pre-ablation inducibility is not required and is discouraged unless in the abovementioned conditions.

### Device programming and medical therapy

All patients involved in the study, regardless of Group allocation, will have their ICD programmed following 2019 HRS/EHRA/APHRS/LAHRS expert consensus statement on optimal ICD programming [11], following the manufacturer specific recommendations about therapy and detection in patients where VT cycle is known, alongside any anti-bradycardia setting necessary for therapeutic needs. Particularly, the VT zone with lower rate detection should be set at 10–20 beats/min slower than the clinical VT to guarantee a good sensitivity in recurrences diagnosis and therapy should be programmed in order to reduce unnecessary shocks.

Patients involved in the study will be treated with antiarrhythmic drugs and any other medical therapy considered standard of care for the SHD and VT. Particularly, use of amiodarone is allowed at enrollment but it is strongly suggested to stop it at 1 month follow-up, if not contraindicated, to avoid drug-related toxicity.

### Follow-up

Clinical follow-up (FU) will include outpatient clinic visits at 1, 6 and 12 months after the ablation procedure. If no contraindications, amiodarone (if used) should be stopped at the 1-month FU visit. At all follow up visits, the following parameters and information will be taken:Physical examination.12-lead surface ECG.Transthoracic echocardiography (at 6 and 12 months).ICD interrogation, analyzing any event marked as VT or VF by the device.

To assess changes in health-related quality of life, the 36-Item Short Form Survey (SF-36) will be administered at enrolment and at the 12-months follow up visit (Table 4).

**Table 4 Tab4:** Study timeline

PROCEDURE	VISIT						
	Enrollment	Baseline	Ablation	Discharge	1 month	6 months	12 months
Eligibility screen	✓						
Informed consent	✓						
Demographic Data		✓					
Medical History		✓					
QoL assessment		✓					✓
Medication		✓		✓	✓	✓	✓
12-lead ECG		✓		✓	✓	✓	✓
CMR (gr. 1 and 2)		✓					
TTE		✓				✓	✓
Cardiac CT (gr. 1 and 2)		✓					
ICD check				✓	✓	✓	✓
Ablation data			✓				
Safety data			✓	✓	✓	✓	✓
Protocol Deviation	✓	✓	✓	✓	✓	✓	✓
Adverse event	✓	✓	✓	✓	✓	✓	✓
Termination	✓	✓	✓	✓	✓	✓	✓

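### The only rule stated for continuous endpoints leaves the baseline SF-36 score unused and picks t or Welch by an F-test: an avoidable loss of precision, and an error rate that moves only if the group sizes drift apart

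*Protocol article*

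**What the plan says.** Three places in the protocol article matter.

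- The secondary endpoint table (under Study hypothesis and primary endpoint) lists "Health-related quality of life changes". The Follow-up section gives the timing: "the 36-Item Short Form Survey (SF-36) will be administered at enrolment and at the 12-months follow up visit". A baseline score is therefore available by design.
- Sample size and statistical analysis gives one general rule for continuous variables: Student's t-test if normal, "Aspin-Welch test if normally distributed with unequal variance demonstrated using Variance-ratio F-test", and Mann–Whitney if not normal. It names no SF-36 analysis and no baseline-adjusted model for any continuous endpoint. The only multivariable model is a Cox model for predictors of the ablation result. The general level is given by "All applicable statistical tests will be 2-sided and will be performed using a 5% significance level".
- The same section plans the main comparison at equal sizes, "considering 50% of group 1–2 (low risk), 50% of group 3 (high risk"). Under Trial design, however, only Groups 1 and 2 are randomised (1:1). Group 3 takes the patients who cannot have the imaging or whose images are not good enough to process. No quota or cap on Group 3 is stated.

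**The concern.** Two features of the general rule are weak choices.

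First, comparing changes without the baseline as a covariate gives up precision that the collected data would provide at no cost. In the comparison with Group 3, where allocation depends on imaging eligibility and image quality, baseline SF-36 may differ between groups. The change-score answer and the baseline-adjusted answer can then differ, and a plan that does not fix one of them leaves a choice open after the data are seen.

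Second, letting an F-test on the same data decide between the pooled t-test and Welch's test makes the procedure a two-stage one. Its error rate can leave 5% when group sizes and SDs both differ. Procedure, fluoroscopy and radiofrequency times fall under the same rule, so the efficiency claims would be touched wherever those variables are treated as normal.

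**Working it through.** **Planned sizes.** Inputs from Sample size and statistical analysis: "103 patients will be necessary with 80% power and 5% type 1 error"; "16% of likelihood of VT recurrences at 12 months in low-risk patients and 44% of likelihood in high-risk patients"; "HR (high risk/low risk of recurrences) of 2.75 (Cox PH, 2-sided equality").

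- Events (Schoenfeld): (1.960 + 0.842)² / (0.25 × (ln 2.75)²) = 30.68.
- Mean event probability: 0.5 × 0.16 + 0.5 × 0.44 = 0.30.
- N = 30.68 / 0.30 = 102.3, so 103. The stated figure reproduces.

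The planned comparison is therefore about 52 against 51, and the randomised one about 26 against 26. No SD, effect size or power is stated for SF-36 or any other continuous endpoint, so everything below rests on assumed values.

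**Precision of SF-36 change.** Take equal SDs (set to 1) at baseline and 12 months, with correlation r.

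- Variance of change: 2(1 − r).
- Residual variance under ANCOVA: 1 − r².
- Ratio: (1 − r²) / (2(1 − r)) = (1 + r)/2.

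| r (assumed) | change | ANCOVA | ratio | SE smaller by |
|---|---|---|---|---|
| 0.4 | 1.20 | 0.84 | 0.70 | 16% |
| 0.5 | 1.00 | 0.75 | 0.75 | 13% |
| 0.6 | 0.80 | 0.64 | 0.80 | 11% |

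Group size does not enter the ratio, so the gain is the same at any split. It presumes no systematic baseline difference, which randomisation secures for Group 1 against Group 2 only.

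**Groups 1–2 against Group 3.** The change-score estimate subtracts the whole baseline difference; ANCOVA subtracts r times it. The two differ by (1 − r) × the baseline difference. For an illustrative imbalance of 0.3 SD that is 0.18, 0.15 and 0.12 SD at r = 0.4, 0.5 and 0.6.

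**F-test step.** Normal data with no true difference were simulated, with at least 100,000 runs per setting. At 200,000 runs the simulation error is √(0.05 × 0.95 / 200,000) = 0.05 percentage points. The rule was Welch if the two-sided F-test gave p < 0.05, and pooled t otherwise. At the planned sizes, over SD ratios from 0.5 to 2, type I error was 4.95–5.04% at 52/51 and 4.95–5.06% at 26/26. At an assumed SD ratio of 1.3:

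| Split | larger SD in smaller group | larger SD in larger group | Welch alone |
|---|---|---|---|
| 52/51 (planned) | 5.0% | 5.0% | 5.0% |
| 72/31 (assumed) | about 6% | 4.2% | about 5% |
| 82/21 (assumed) | 7.1% | 3.8% | about 5% |

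A milder drift to 62/41 with the larger SD in the smaller group gives about 5.5%.

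**The case against.** The strongest reply is that no sentence says how SF-36 will be tested. The article condenses a fuller plan, and baseline adjustment of a patient-reported secondary outcome is commonly left to the SAP. That stands as a limit: the unadjusted test is inferred from the general rule, and an absent covariate would not by itself be a fault. What remains is that the article states a rule for continuous variables without exception. An SAP that adjusts would depart from it, so the rule is worth correcting where it stands. The F-test step needs no inference.

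Three stronger readings are tempting, and the document supports none of them.

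- A reader might infer that the planned secondary comparisons have a wrong error rate. At 50/50 and 1:1 they do not. Inflation needs both a drift in group sizes and the larger SD in the smaller group. The document gives no figure for the eventual share of Group 3, which could go either way, and the reverse pattern makes the rule conservative. Variables sent to Mann–Whitney bypass the F-test altogether, which may include the procedural times if they are skewed.
- A reader might infer that ANCOVA makes the comparison with Group 3 fair. When true baseline means differ, change scores and ANCOVA answer different questions (Lord's paradox), and which is unbiased depends on assumptions that the data cannot test. Adjusting for baseline SF-36 does not remove other confounding.
- A reader might tie the precision loss to unequal groups. It does not depend on the split.

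**Conclusion.** The point holds in a limited form. Read as written, the rule leaves the baseline SF-36 score unused as a covariate. In the randomised comparison this costs precision: change scores have 1/0.80 to 1/0.70, or about 1.25 to 1.43 times, the ANCOVA variance at r = 0.6 to 0.4. In the non-randomised comparison the gain is not assured, and the reason to prespecify is that two defensible analyses may differ by an amount that matters. The F-test step has no effect at the planned sizes and a modest effect in either direction if the sizes drift, while Welch alone is close to 5% at every split tried. The correlations, the SD ratio, the unequal splits and the 0.3 SD imbalance are assumptions, not figures from the article. Only secondary endpoints are affected; the primary analysis and the 103 patients are untouched. This is a desirable refinement, not a flaw that threatens the trial.

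**What to change.** 1. State that 12-month SF-36 scores are analysed by ANCOVA with the enrolment score as covariate, for Group 1 against Group 2 and for Groups 1–2 against Group 3.
2. Label the second comparison as non-randomised, and say that adjustment for baseline SF-36 is not claimed to remove confounding.
3. Use Welch's test for all other approximately normal continuous endpoints and delete the variance-ratio F-test step. Mann–Whitney for non-normal variables can stay.

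The cost is analysis wording only: no new data, visits or patients, and no change to the primary analysis or sample size. The downside is negligible, since Welch holds 5% at the planned equal sizes too.
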